**CONCLUSION::**

Since the HSR response is decreased in individuals with diabetes, we believe that improving the HSR may be important in preventing chronic complications associated with T2DM. This randomized clinical trial will determine the efficacy of HT compared to RT in improving HSR when combined with conventional therapy in individuals with T2DM. Multiple HT and RT effects may contribute to a lower mortality risk in these individuals.

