### Statistical considerations

To assess the effect of exercise on plasma HSP levels between the groups post-intervention, we assumed 80% power, 5% significance level, and an effect size (Cohen’s F) of 0.4. We estimated a dropout rate of 10%, and the calculated total number of patients was 22 in each group.^
24
^

The randomly assigned participants’ data will be analyzed according to the intention-to-treat principle as the primary choice and the per-protocol principle, with treatment, time, and treatment-time interaction registered as fixed effects. We will qualitatively document the reasons for, and details of, each withdrawal case. The normality of the data will be tested using the Shapiro-Wilk test. Mean and standard deviation will be used to describe parametric continuous variables, with median and interquartile range for non-parametric variables, and absolute and relative frequencies for categorical variables. Analysis of variance (ANOVA) will be used to compare the final outcomes. Treatment effects (group, time, and group interaction) will be estimated using Generalized Estimation Equations (GEE), followed by the Bonferroni post-hoc test (P < 0.05). Multiple linear regression analysis (backward method) will be performed to investigate the impact of routine pharmacotherapy, sex, and age on the primary and secondary outcomes. SPSS Professional software (version 20.0; IBM Corp., Armonk, New York, United States) will be used for all analyses.

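### The 80% power fits only the overall three-group test; the pairwise comparisons behind the trial's conclusions, tested with Bonferroni, were not separately powered and fall short of 80% on post-intervention values

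*Protocol article*

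**What the plan says.** All references are to the Protocol article. Under Statistical considerations, the aim of the sizing is given as "To assess the effect of exercise on plasma HSP levels between the groups post-intervention". The assumptions are "we assumed 80% power, 5% significance level", "and an effect size (Cohen’s F) of 0.4", and a 10% dropout rate. The result is that "the calculated total number of patients was 22 in each group". The test that was sized is not named.

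The same section plans an ANOVA of the final outcomes. It also plans GEE with group, time and their interaction, "followed by the Bonferroni post-hoc test" at P < 0.05. It gives no pairwise effect size, no pairwise power and no number of post-hoc comparisons.

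The abstract's conclusion states: "This randomized clinical trial will determine the efficacy of HT compared to RT in improving HSR". The Discussion says much the same. The Objective section sets out to compare RT with HT and hypothesizes that both will work. Study design and setting also calls the trial non-inferiority; the article states no margin.

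**The concern.** Cohen's f is an effect size for a test that several means are all equal. A significant overall test says only that the three arms differ somewhere. It does not say that RT beats control, that HT beats control, or how HT compares with RT. Each of those statements needs a pairwise contrast, and the Bonferroni post-hoc is the only pairwise procedure that the article names.

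The only power figure in the article is 80%, so readers are likely to carry it over to the pairs. They would then give a non-significant pairwise result more weight than it deserves. The risk is greatest for HT versus RT: with a non-inferiority label on the design, a non-significant difference could be reported as HT being as good as RT.

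**Working it through.** **Inputs.** From Statistical considerations: f = 0.4, 5% significance, 22 per arm, 10% dropout. From Interventions: three arms. Assumed, because the article does not say: equal arms, three pairwise comparisons, two-sided tests, pooled variance, and a comparison of post-intervention values as in the sizing sentence. It is unclear whether 22 already includes dropout. If it does, 22 × 0.9 ≈ 20 remain, so both 20 and 22 are shown.

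**Step 1: reproduce the plan's figure.** The overall F test has 2 and 3n − 3 degrees of freedom and noncentrality λ = 3n·f².

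| n per arm | λ | critical F | power |
|---|---|---|---|
| 20 | 60 × 0.16 = 9.60 | 3.159 | 77.6% |
| 21 | 63 × 0.16 = 10.08 | 3.150 | 79.8% |
| 22 | 66 × 0.16 = 10.56 | 3.143 | 81.8% |

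22 is the smallest n that reaches 80%, so the stated size matches the overall test.

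**Step 2: turn f into pairwise differences d (in SD units).**
- One arm differs from two equal arms: d = 3f/√2 = 1.2/1.414 = 0.849.
- Evenly spaced means: outer pair d = f√6 = 0.4 × 2.449 = 0.980; each adjacent pair 0.490.

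For three means with a given f, f√6 is the largest difference that any pair can have.

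**Step 3: Bonferroni pairwise power.** Noncentral t with 3n − 3 degrees of freedom, noncentrality d·√(n/2), level 0.05/3 = 0.0167. The critical t is 2.467 at n = 20 and 2.460 at n = 22.

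| d | noncentrality, n = 20 / 22 | power, n = 20 / 22 |
|---|---|---|
| 0.849 | 2.683 / 2.814 | 58.8% / 63.9% |
| 0.980 | 3.098 / 3.250 | 73.4% / 78.3% |
| 0.490 | 1.549 / 1.625 | 18.9% / 21.0% |

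**Step 4: assign these to the comparisons.**

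| Pattern | Active arm vs control | HT vs RT |
|---|---|---|
| HT = RT, both differ from control | 59–64% each | no difference to detect (1.7% is type I error) |
| Even spacing, control at one end | better arm 73–78%, other arm 19–21% | 19–21% |
| Only one arm works | that arm 59–64% | 59–64% |
| Even spacing, control in the middle | 19–21% each | 73–78% |

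Even the largest possible pairwise difference stays below 80%.

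**Step 5: sensitivity, for d = 0.849.** At 20 to 22 per arm, two comparisons give 65–70%, and all 15 pairs of the six group-by-time cells give 36–41%. At n = 20, with three comparisons of change scores, assumed pre-post correlations of 0.3, 0.5 and 0.7 give 43%, 59% and 84%.

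**Step 6: closed testing.** Pairs are tested at 5% only if the overall test is significant at 5%. By simulation at n = 20 and 22, power for a pair with d = 0.849 is about 69–75%, against 59–64% with Bonferroni. For adjacent pairs (d = 0.490) it is 32–35%, against 19–21%. Simulated family-wise error is about 5%, both when all three means are equal and when one pair is equal.

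**The case against.** **No stated figure is wrong.** The article never claims 80% for a pair, and 22 per arm reproduces for the test that f implies. That stands. A reader might infer a miscalculated sample size or a false pairwise claim; the text supports neither. The gap lies between what was sized and what the trial says it will conclude.

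**The pairwise figures depend on the pattern.** That stands too. A reader might infer that HT versus RT always has about 20% power. It has 19–21% only with even spacing and control at one end, and 59–64% if only one arm works. The 59–64% against control and the 19–21% for HT versus RT come from different patterns and must not be quoted as one result.

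**The named post-hoc follows GEE on baseline and week-12 data, whereas the calculation uses post-intervention values only.** This is correct, and it is why no single pairwise figure belongs in the protocol. In the change-score check, only the assumed correlation of 0.7 lifted the power above 80%.

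**The non-inferiority label may govern HT versus RT.** If so, superiority power is not the relevant quantity, and the relevant one cannot be computed without a margin. The figures here are for superiority only.

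**Bonferroni is valid.** It is, and its use is not an error. With exactly three group contrasts it is more conservative than it needs to be. Replacing it is an inexpensive improvement, and it does not bring the pairs checked at d = 0.849 or 0.490 up to 80%.

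**Conclusion.** The point holds in a limited form. The 80% belongs to the overall three-group comparison, and the pairwise contrasts that the trial's conclusions need were not separately powered. With three two-sided Bonferroni comparisons of post-intervention values at f = 0.4 and 20 to 22 per arm, no pair reaches 80%. Power runs from 19–21% to 73–78% where a difference of the sizes examined exists. The number of comparisons and the pre-post correlation are not stated, and either can move the figures substantially in either direction. A non-significant HT–RT result therefore cannot be read as equivalence or non-inferiority.

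**What to change.** 1. State under Statistical considerations that the 80% refers to the overall three-group comparison, and that pairwise comparisons, HT versus RT in particular, were not separately powered. Give any pairwise power as a range with its assumptions (pattern of means, number of comparisons, pre-post correlation), not as a single value.
2. For the three between-group superiority contrasts on the primary outcome (group differences in the group-by-time effect), replace Bonferroni by closed testing: pairwise tests at 5%, only if the global test with 2 degrees of freedom is significant at 5%. Show Bonferroni intervals alongside.
3. Limit this rule to those three contrasts. It does not carry over to comparisons across all six group-by-time cells, nor to any non-inferiority claim.
4. State that a non-significant HT–RT difference will not be interpreted as equivalence.

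The cost is wording and a changed test sequence, with no additional patients. The power statement becomes less favourable, and closed testing itself gives no simultaneous confidence intervals, which is why the Bonferroni intervals are kept.

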### Allocation

Participants will be randomly assigned to groups according to a sequence of computer-generated random numbers. This sequence will be obtained in Microsoft Excel (Redmond, Washington, United States) in a 1:1 ratio, with blocks of eight or six participants to complete the total number calculated. A sealed envelope containing the allocation code will be opened at the beginning of the treatment in the presence of the participant according to the order of entry into the study.

Owing to the nature of the interventions, the researcher conducting the exercise sessions and participants will not be blinded. To ensure assessor masking, the participants will be asked to omit their assigned groups and not talk about their interventions during the outcome evaluation sessions. In case of unintentional unblinding for any reason, the researcher will notify the principal researcher.

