### Interventions

Volunteers who met the inclusion criteria will be guided through the study and asked to sign a written informed consent form before enrollment in the trial. The participants will be randomized into the following intervention groups: control, RT or HT. In the control group, participants will not receive any intervention. In the intervention group RT, participants will perform supervised exercises in a gymnasium on three non-consecutive days of the week for a total of 12 weeks. Each session will last approximately 60 min and consist of warm-up, resistance training, and cool-down. All sessions will be conducted by qualified sports and exercise scientists.

The RT program will consist of a combination of upper- and lower-body exercises using gymnasium equipment, free weights, and body weight (functional exercises) as the primary resistance. The 12 weeks RT will be divided into three mesocycles of four weeks each (please see details of sets, repetitions, and intervals in Table 1). The exercises will include leg press, knee extension, leg curl, biceps curl, triceps extension, lat pulldown, shoulder press, bench press, and abdominal crunch exercises. Before the start of the training period, the participants completed a familiarization session to practice the exercises they would perform further during the training program when the exercise load was individually tested. Resistance training was performed using two–three sets per exercise at intensities between 12 and 15 maximum repetitions (the heaviest possible weight to perform 12–15 repetitions), as shown in Table 1. The intensity of the functional exercises was controlled using the OMNI scale,^
21
^ with each session lasting 60 min.

**Table 1 T1:** Resistance training program

Mesocycle	Weeks	Repetitions/load	Number of sets	Interval between sets
**1**	1–4	12/15	2	1 min
**2**	5–8	12/15	3	1 min
**3**	9–12	10/12	3	1 min and 30 s

Participants in the HT group will undertake whole body heat treatment according to previous methods.^
22

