### Data collection and management

A questionnaire will be employed to obtain the sociodemographic and clinical characteristics of the participants, including age, sex, marital status, schooling level, diabetes duration, family history of diabetes, use of antimicrobials in the last 30 days, and self-reported physical activity. T2DM drugs will be recorded at baseline and end of the study period.

Anthropometric measures, including body weight, height, calculated body mass index (kg/m^2^), waist circumference, and hip circumference changes will be recorded at the first and last visits. Weight will be measured using a digitally calibrated balance with a maximum capacity of 150 kg and a precision of 100 g. The height will be determined by a vertical statometer attached to the balance with a capacity of 2 m/0.1 cm (Urano, Canoas, Brazil). Waist and hip circumferences will be measured using an inelastic metric tape (2 m/0.1 cm). The total corporal composition will be evaluated using dual-energy X-ray absorptiometry (DEXA scan, Lunar iDXA, GE Healthcare, Buckinghamshire, United Kingdom).

After this evaluation, individuals will perform a self-limited maximal exercise test on a treadmill to determine peak oxygen uptake (VO_2_ peak) and peak HR, supervised by a team of experienced exercise physiologists. The test will be carried out according to the Bruce protocol.^
25
^ Oxygen uptake (VO_2_) and carbon dioxide production (VCO_2_) were determined using a breath-by-breath computerized gas exchange system and analyzed using a 20-second averaging signal. The basal metabolic rate will be analyzed in a fasting state (Quark CPET, Cosmed, Italy).

At the first and last visits to the laboratory, blood samples will be collected and centrifuged at 1,000 × g for 10 min to separate the plasma, which will be stored for further analysis of biochemical parameters. The total glucose, C-reactive protein, HDL cholesterol, HbA1c, and triglyceride levels will be determined using an automated Cobas C111 system (Roche Diagnostics, Basel, Switzerland). LDL-cholesterol will be calculated by the Fried Ewald equation.^
26
^ Insulin resistance was calculated using the Homeostatic Model Assessment (HOMA-IR) method based on insulin and fasting glucose levels.^
27
^

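### Backward elimination in the supplementary regression on drugs, sex and age will report surviving terms with P values and standard errors that ignore the selection.

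*Protocol article*

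**What the plan says.** Statistical considerations describes two separate pieces of analysis. The randomised comparison is one: "Treatment effects (group, time, and group interaction) will be estimated using Generalized Estimation Equations (GEE), followed by the Bonferroni post-hoc test". ANOVA is also named for the final outcome values. No covariate selection is attached to either.

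The other is a regression on patient characteristics: "Multiple linear regression analysis (backward method) will be performed to investigate the impact of routine pharmacotherapy, sex, and age". Its scope is "routine pharmacotherapy, sex, and age on the primary and secondary outcomes". The article gives no removal level, no number or coding of drug terms and no allowance for the selection. The Bonferroni step belongs to the GEE, not to this regression.

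On size: "We estimated a dropout rate of 10%, and the calculated total number of patients was 22 in each group". On the drug data, Data collection and management says: "T2DM drugs will be recorded at baseline and end of the study period".

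**The concern.** Backward elimination starts from all candidates and discards those that look weak. The final model is then read as if its terms had been fixed in advance. Each surviving term has passed a significance screen on the same data, yet its P value, standard error and interval are computed as though no screen had taken place. Estimates that happen to be large survive and small ones disappear, so what remains is biased away from zero.

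The stated purpose is to learn how drugs, sex and age bear on the outcomes, so the reported coefficients are themselves the result. Readers could be told that a drug class, sex or age influences the heat shock response or a secondary marker, with more certainty and a larger effect than the data support. The retained set can also differ from outcome to outcome, which makes the models hard to compare.

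**Working it through.** **Inputs from the protocol article.** Three groups of 22; 10% dropout; 5% significance; 80% power; Cohen's f = 0.4; backward method; candidates drugs, sex and age.

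**Assumptions, because the article does not fix them.** Removal at P of 0.10 or above; drugs coded as 1, 3 or 6 indicators, giving 3, 5 or 8 candidates with age and sex; candidates uncorrelated or correlated at 0.3.

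**Step 1: the plan's own figure.** For a one-way ANOVA with three groups and noncentrality f² × N, 22 per group (N = 66) has power 0.818 and 21 per group has 0.798. So 22 reproduces as the smallest sufficient size before any allowance for loss. With 10% loss, 66 × 0.90 = 59.4, or about 60 completers.

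**Step 2: approximate arithmetic for one null term.** Its P value is roughly uniform. It is retained if P < r, and its 95% interval covers zero if P is at least 0.05. Coverage given retention is therefore about (r − 0.05)/r:

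- r = 0.05: 0%
- r = 0.10: 0.05/0.10 = 50%
- r = 0.20: 0.15/0.20 = 75%
- r = 1 (no elimination): 95%

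None of these screening levels restores 95%. The chance that at least one of k independent null terms is retained at r = 0.10 is 1 − 0.9^k, which is 27%, 41% and 57% for k = 3, 5 and 8.

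**Step 3: simulation, N = 60.** There were 2,000 data sets per setting. Least-squares models with group terms plus the candidates were fitted by backward elimination and, for comparison, in full without selection. All covariate effects are null in the table.

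| Candidates | At least one false P < 0.05, backward | Same, full model | 1 − 0.95^k |
|---|---|---|---|
| 3 | 14–15% | 14% | 14% |
| 5 | 25–28% | 22–23% | 23% |
| 8 | 37–40% | 30–32% | 34% |

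- The excess due to selection is about 1 point with three candidates and 7 to 8 points with eight. A separate simulation put the latter at about 5, so 5 to 8 is a fair range.
- The false-positive rate per coefficient is 5.3 to 6.8% after selection, against about 5% in the full model.
- Nominal 95% intervals of retained null terms cover zero in about 45 to 50% of cases with uncorrelated candidates, as Step 2 predicts. With correlation 0.3 the figure falls as low as 42%.

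**Step 4: a real effect.** A true effect of 0.25 SD per SD of age is retained in about 58 to 60% of runs. When retained, its mean estimate is about 0.34, and 0.34/0.25 = 1.36, an overestimate of about 35%. Coverage of its interval stays at 94 to 95%.

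**Step 5: sensitivity to dropout.** N = 66 gives the same pattern.

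**Step 6: after the fix.** In the full model the false-positive rate per coefficient is 4.7 to 5.6%, which is nominal. With three covariate terms, the chance of at least one false finding per outcome stays at about 14%.

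**The case against.** The strongest reply is that this regression is a side analysis of three named factors and that selection does little harm to it. Much of that stands.

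- A reader might infer that the treatment effects are compromised. They are not: they come from GEE and ANOVA, for which no selection is described.
- A reader might infer that randomised group could be eliminated from the model. The article names only drugs, sex and age as the factors studied. Even if group terms could be dropped, their type I error would be 6.4 to 7.0% instead of about 5%.
- A reader might infer that end-of-study drug use, which the interventions could influence, will serve as a covariate. The article says only that it is recorded, and recording is not modelling.
- A reader might take the whole 14 to 40% in the table as the price of backward elimination. Most of it is multiplicity from testing several covariates, which the full model shares.
- The number of drug terms is not stated. With one drug variable the excess is about 1 point.

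It is also true that 50% coverage would follow from any rule that reports only terms with P < 0.10. That does not rescue the method, because reporting only the survivors is what a backward-selected final model does. Nor can the point be set aside as detail left to a fuller plan: the article itself names the selection method.

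**Conclusion.** The point holds for the supplementary covariate regression and no further. The harm lies mainly in what is reported for retained terms. Null terms that survive have intervals covering zero about 45 to 50% of the time instead of 95%, and a modest real effect is overstated by about 35%. The overall false-positive rate per outcome moves much less, by about 1 point with three candidates and 5 to 8 with eight.

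These sizes rest on the assumed removal level of 0.10, the assumed number of drug terms and the assumed true effect of 0.25 SD. The direction does not depend on the exact level, as Step 2 of the working shows. The documents give no ground for extending the criticism to the randomised comparison.

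**What to change.** In Statistical considerations, replace the backward method by one fixed linear model per outcome. It should contain age, sex and one pre-named baseline pharmacotherapy variable (for example the number of glucose-lowering drugs), with randomised group and the baseline value of the outcome forced in. Report every coefficient with its interval, without selection, and label the analysis exploratory. State that the treatment effect continues to be taken from the GEE, so that this model does not become a second estimate of it. Naming the baseline time point also settles which of the two drug records is meant.

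The exploratory label is needed because a fixed model removes the selection bias but not the multiplicity over covariates and outcomes.

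The cost is a change of wording and a few degrees of freedom spent on terms that may prove uninformative. No new data or participants are needed.

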### Data collection and management

A questionnaire will be employed to obtain the sociodemographic and clinical characteristics of the participants, including age, sex, marital status, schooling level, diabetes duration, family history of diabetes, use of antimicrobials in the last 30 days, and self-reported physical activity. T2DM drugs will be recorded at baseline and end of the study period.

Anthropometric measures, including body weight, height, calculated body mass index (kg/m^2^), waist circumference, and hip circumference changes will be recorded at the first and last visits. Weight will be measured using a digitally calibrated balance with a maximum capacity of 150 kg and a precision of 100 g. The height will be determined by a vertical statometer attached to the balance with a capacity of 2 m/0.1 cm (Urano, Canoas, Brazil). Waist and hip circumferences will be measured using an inelastic metric tape (2 m/0.1 cm). The total corporal composition will be evaluated using dual-energy X-ray absorptiometry (DEXA scan, Lunar iDXA, GE Healthcare, Buckinghamshire, United Kingdom).

After this evaluation, individuals will perform a self-limited maximal exercise test on a treadmill to determine peak oxygen uptake (VO_2_ peak) and peak HR, supervised by a team of experienced exercise physiologists. The test will be carried out according to the Bruce protocol.^
25
^ Oxygen uptake (VO_2_) and carbon dioxide production (VCO_2_) were determined using a breath-by-breath computerized gas exchange system and analyzed using a 20-second averaging signal. The basal metabolic rate will be analyzed in a fasting state (Quark CPET, Cosmed, Italy).

At the first and last visits to the laboratory, blood samples will be collected and centrifuged at 1,000 × g for 10 min to separate the plasma, which will be stored for further analysis of biochemical parameters. The total glucose, C-reactive protein, HDL cholesterol, HbA1c, and triglyceride levels will be determined using an automated Cobas C111 system (Roche Diagnostics, Basel, Switzerland). LDL-cholesterol will be calculated by the Fried Ewald equation.^
26
^ Insulin resistance was calculated using the Homeostatic Model Assessment (HOMA-IR) method based on insulin and fasting glucose levels.^
27
^

To analyze the gut microbiota, genomic DNA will be extracted from 0.25 g of homogenized fecal samples using the QIAamp PowerFecal Pro DNA Kit (Qiagen, United States), according to the manufacturer’s instructions. The quality of the DNA will be evaluated by agarose gel electrophoresis and purity will be assessed by the 260/280 nm and 260/230 nm ratios measured using a NanoDrop 1000 instrument (Thermo Fisher Scientific, Waltham, MA, United States). DNA concentration will be quantified using Qubit dsDNA Reagent (Molecular Probes, Thermo Fisher Scientific Division, Eugene, OR, United States). The V3-V4 hypervariable region of the 16S rRNA gene will be amplified and sequenced using Illumina MiSeq V3 kit (2 × 300 cicles). The preprocessing and follow analysis will be conducted in R within the RStudio platform, using software package DADA2 for taxonomic assignment (with the SILVA ribosomal RNA gene database).^
28-31
^

For inflammatory biomarkers and plasma LPS levels, patientblood will be centrifuged at 1,000 g for 10 minutes and serum will be frozen (−80°C) for further analysis by the enzyme-linked immunosorbent assay (ELISA) technique, using commercial kits for: LPS, TNF-α, IL-1, IL-4, IL-5, IL-6, IL-10, and IL-13 (Human ELISA Kits, Sigma-Aldrich, St. Louis, MI, United States).

Considering the importance of HSR in stress adaptation, we will test the capacity of leukocytes (a major source of circulating HSP72 and representative of the immune cell stress response) to release HSP72 under heat stress conditions (a physiological and expected response in healthy cells). We will use this strategy to compare whether different interventions can improve HSR in patients with diabetes. Briefly, after harvesting, whole blood will be immediately incubated at two different temperatures: 37°C (control) and 42°C (heat stressed) for 2 h in a water bath. After incubation, the total blood will be centrifuged to isolate the plasma. Plasma will be used for the analysis of extracellular HSP72.^
32
^ A highly sensitive, enzyme-linked immunosorbent assay (EIA) method (EKS-715 Stressgen, Victoria, Canada) will be used to quantify the levels of plasma HSP72 protein, as previously described.^
33
^ Inflammatory cell signaling in PBMC (NF-κB; TLR2 e 4, TRIF, IKKi/IKKε, and MyD88) will be analyzed by western blot, as previously described.^
34
^

